## Abstract

**Background:**

Home-based (unsupervised) buprenorphine initiation is considered safe and effective, yet many patients report barriers to successful treatment initiation. Prescription digital therapeutics (PDTs) are software-based disease treatments regulated by the US Food and Drug Administration (FDA). The reSET-O PDT was authorized by the FDA in 2018 and delivers behavioral treatment for individuals receiving buprenorphine for opioid use disorder (OUD). A prototype PDT (PEAR-002b) designed for use with reSET-O was developed to assist in unsupervised buprenorphine initiation.

**Objective:**

The primary objective of this pilot study is to evaluate the acceptability of PEAR-002b in individuals with OUD who use it to support buprenorphine initiation, their unsupervised buprenorphine initiation success rate, and their medication adherence.

**Methods:**

Ten adults with OUD will be recruited for acceptability and feasibility testing. Outcomes will be assessed using week-1 visit attendance, participant interviews and satisfaction surveys, and urine drug screening (UDS). Three tools will be used in the study: PEAR-002b, reSET-O, and EmbracePlus. PEAR-002b includes a new set of features designed for use with reSET-O. The mechanism of action for the combined PEAR-002b and reSET-O treatment is a program of medication dosing support during week 1 of the initiation phase, cognitive behavioral therapy, and contingency management. During the medication initiation phase, participants are guided through a process to support proper medication use. PEAR-002b advises them when to take their buprenorphine based on provider inputs (eg, starting dose), self-reported substance use, and self-reported withdrawal symptoms. This study also administers the EmbracePlus device, a medical-grade smartwatch, to pilot methods for collecting physiologic data (eg, heart rate and skin conductance) and evaluate the device’s potential for use along with PDTs that are designed to improve OUD treatment initiation. Home buprenorphine initiation success will be summarized as the proportion of participants attending the post–buprenorphine initiation visit (week 1) and the proportion of participants who experience buprenorphine initiation–related adverse events (eg, precipitated withdrawal). Acceptability of PEAR-002b will be evaluated based on individual participants’ ratings of ease of use, satisfaction, perceived helpfulness, and likelihood of recommending PEAR-002b. Medication adherence will be evaluated by participant self-report data and confirmed by UDS. UDS data will be summarized as the mean of individual participants’ proportion of total urine samples testing positive for buprenorphine or norbuprenorphine over the 4-week study.

**Results:**

This project was funded in September 2019. As of September 2022, participant enrollment is ongoing.

**Conclusions:**

This is the first study to our knowledge to develop a PDT that assists with unsupervised buprenorphine initiation with the intent to better support patients and prescribers during this early phase of treatment. This pilot study will assess the acceptability and utility of a digital therapeutic to assist individuals with OUD with unsupervised buprenorphine initiation.

**Trial Registration:**

ClinicalTrials.gov NCT05412966; https://clinicaltrials.gov/ct2/show/NCT05412966

**International Registered Report Identifier (IRRID):**

PRR1-10.2196/43122

## Introduction

Unprecedented rates of opioid misuse and mortality have led to the current opioid epidemic in the United States [1], with approximately 2.5 million people in the United States meeting the criteria for opioid use disorder (OUD) in 2020 [2]. OUD is a chronic condition with numerous physical, psychological, and personal consequences, including a high risk of death, which has risen in recent years due to the increasing prevalence of potent synthetic opioids (predominantly fentanyl) [3]. According to the latest reports, 74,754 adults died from opioid-related overdoses in the 12 months ending September 2021, representing a daily average of 205 deaths [1], a 55% increase since September 2019 [4]. Opioid-related overdoses now account for 75% of fatal overdoses of all substances, up from 70.6% in 2019, with synthetic opioids accounting for 86.6% of opioid-related deaths [4].

Initiation of evidence-based medications for opioid use disorder (MOUD), such as buprenorphine, methadone, or naltrexone, remains limited; in 2020, only 11.2% of those with OUD received MOUD treatment [2]. One of the key barriers is limited access to MOUD treatment [2], which is amplified by health care provider reservations about prescribing buprenorphine for OUD. Key reasons for this hesitancy include logistical barriers, perceptions that people with addiction are difficult to treat, insufficient time and staff support, limited provider and staff knowledge and training, and lack of a support network of experienced prescribers [5-8]. Despite the recent removal of the “X waiver” training requirement, prescribers may still feel they are not adequately equipped to begin prescribing for the above reasons [9].

For individuals who do access MOUD, medication adherence is unsatisfactory, and medication discontinuation rates are high [10,11]. Buprenorphine discontinuation rates at 6 months range from 50% to 65%, with most discontinuations occurring within the first 3 months of treatment, particularly within the first 30 days, which is a crucial phase that includes initiation and titration of buprenorphine to achieve dose stabilization [10-14]. Evidence from different real-world settings suggests that MOUD discontinuation is estimated to increase the likelihood of relapse by roughly 10 times, with relapse being strongly associated with overdose and death [15-17].

The medication initiation phase for buprenorphine, in particular, is critical. Patients who have negative experiences initiating buprenorphine may not continue treatment beyond the first day of dosing [18]. Successful initiation of buprenorphine requires the patient to be in mild to moderate withdrawal before they begin the medication [19]. People’s desire to avoid experiencing withdrawal symptoms is a primary reason they continue to use and can be a major barrier to beginning treatment [20]. Buprenorphine initiation is a high-touch process for clinicians that requires educating the patient on not only the risks and benefits of buprenorphine, but how the medication works, when to start treatment, and how to manage emotions like fear and anxiety that can complicate the process.

Providing an accessible tool that supports both the patient and clinician by offering education as well as motivational and skills-based support during this important phase of treatment could enhance the patient experience and help improve clinician willingness to prescribe. Unsupervised buprenorphine initiation, whether supported via telemedicine or traditional in-person provider interactions, is considered safe and effective and may be an equitable and accessible way to increase the rate of successful MOUD initiation [19]. One potential limitation of unsupervised MOUD initiation is the inability of physicians to monitor patient biometrics (eg, pulse, blood pressure, and oxygen saturation levels), which can inform treatment and dosing decisions. New devices exist to monitor biometrics, but whether unsupervised buprenorphine initiation protocols could benefit from data collected by passive biometric monitoring is unknown.

Another technology that may potentially be leveraged to improve the MOUD initiation process is prescription digital therapeutics (PDTs), which are software-based disease treatments evaluated for safety and effectiveness in randomized controlled trials and authorized by the US Food and Drug Administration (FDA). Prescribed by treating physicians and delivered on mobile devices, PDTs can expand access to evidence-based behavioral therapies across a variety of disease states, including OUD.

The reSET-O PDT was authorized by the FDA in 2018 for patients with OUD being treated with buprenorphine. The PDT delivers two evidence-based mechanisms of action: (1) an OUD-specific form of cognitive behavioral therapy (CBT) based on the community reinforcement approach, delivered as on-demand lessons and interactive text, video, and audio exercises and (2) reinforcement and motivation for lesson completion and abstinence via contingency management (CM), which involves eligibility for positive reinforcement messages or monetary digital gift cards. Moreover, there is currently no FDA-authorized PDT that provides assistance with home initiation of MOUD. Opportunities thus exist to better support patients with OUD in the medication initiation phase and to provide strategies to lower potential barriers to the implementation of buprenorphine MOUD treatment in clinical practice.

Given the importance of buprenorphine adherence and the need to better support both patients and providers during the initiation process, we are conducting a pilot study to evaluate PEAR-002b, an investigational digital therapeutic intended to be used with reSET-O and designed to support patients during unsupervised initiation of buprenorphine. The study also includes a wearable device capable of capturing and transmitting biometric data to evaluate the feasibility of biomarker development.

## Methods

### Study Objectives

The objective of this pilot study is to evaluate device acceptability, home buprenorphine initiation success rate, and medication adherence rate among participants with OUD who use the PEAR-002b investigational tool.

### Study Design

This will be a qualitative observational cohort study with a recruitment goal of 10 adults with OUD (inclusion and exclusion criteria are listed below).

### Study Population and Sample Size

The trial will recruit 10 adults diagnosed with OUD. The investigator will ensure that participants being considered for the study meet all eligibility criteria (details are provided in the Study Procedures and Assessments section). No additional criteria will be applied by the investigator to ensure the study population will be representative of all eligible participants. Participants may undergo rescreening with approval of the medical monitor. Due to the exploratory nature of the study, no formal sample size calculations are required.

### Inclusion Criteria

Study inclusion criteria are as follows: written informed consent provided prior to the performance of any study-specific assessments; age ≥18 years; English proficiency sufficient to meaningfully participate in the consent process, assessment, and intervention; a *Diagnostic and Statistical Manual of Mental Disorders, Fifth Edition* (*DSM-5*) diagnosis of OUD made by a treating clinician; desire to start buprenorphine treatment; capability of using common software applications on an internet-enabled mobile device (smartphone or tablet); interest in testing or using PEAR-002b; no prior history of reSET-O use; no participation in investigational drug trials within the past 30 days (or within 5 half-lives of any study drug, whichever is longer) of enrollment; and a judgment that the subject is appropriate for participation by the treating clinician.

### Exclusion Criteria

Study exclusion criteria are as follows: currently on methadone or naltrexone pharmacotherapy; currently on buprenorphine MOUD treatment; planning to move out of the geographic area within 2 months; insufficient English fluency to participate in the consent process, intervention, or assessment; inability to comply with study procedures due to physical or mental condition; currently receiving inpatient treatment for OUD; and pregnancy.

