### Study Procedures and Assessments

Prospective participants referred to the study will be screened for eligibility criteria by a research assistant based on the study inclusion and exclusion criteria and clinical documentation of assessments as needed. Diagnoses of OUD will be made by treating clinicians following standard clinical protocols at the study site, based on *DSM-5* criteria. Recruited participants will be given standard screenings in accordance with the assessment schedule. For the convenience of participants, screening and baseline visits may be combined. All participants will be required to sign an informed consent form at the screening visit, prior to the start of any study procedures. Participants meeting eligibility criteria will be assigned a subject identification number during the baseline visit. Study participants will continue to receive standard treatment for OUD following prescriber-recommended instructions for medication formulation and starting dose, as well as clinic visits unrelated to the study (eg, for medication management or counseling). Standard treatment will be supplemented with the therapeutic tools (PEAR-002b and reSET-O).

Participants will be enrolled for 4 weeks to assess the acceptability and ease of use of the PDT. At baseline, if participants still meet all inclusion and exclusion criteria, study staff will provide them with a phone preloaded with the study apps. Participants will be asked if they also agree to wear the EmbracePlus smartwatch for the duration of the study, and those who agree will be provided the device. Study staff will train willing participants in use of the study apps and the EmbracePlus device. Additionally, a UDS will be performed, and the Clinical Opiate Withdrawal Scale (COWS) will be used. One week later, the participant will return to the clinic and complete a survey and an interview. Study staff will conduct another UDS, administer the COWS, and ask about any adverse events (AEs) or side effects. Following this visit, the participant will return weekly for a UDS and AE assessment. At week 4, the participant will return for a UDS and complete a final survey and exit interview. Primary, secondary, and exploratory objectives and end points are outlined in Textbox 1.

Study objectives and end points.

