#### Primary End Points

Home buprenorphine initiation success will be summarized as the proportion of participants attending the post–buprenorphine initiation visit (week 1) and the proportion of participants who experience buprenorphine initiation–related AEs (eg, precipitated withdrawal). Acceptability of PEAR-002b will be evaluated based on individual participants’ ratings of ease of use, satisfaction, perceived helpfulness, and likelihood of recommending PEAR-002b. Descriptive statistics will be performed on Likert-scale and multiple-choice items that assess user satisfaction and attitudes about the app. Analyses will be conducted on data collected at each assessment point throughout the study, ratings over the course of the study, and for overall user satisfaction as measured at the end of the study. Medication adherence will be evaluated by participant self-report data and confirmed by UDS (ie, a positive result for buprenorphine and norbuprenorphine). UDS data will be summarized as means of individual participants’ proportion of total urine samples testing positive for buprenorphine or norbuprenorphine over the 4-week study.

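### People already using non-prescribed buprenorphine can enter and be counted as initiators, and the day-0 urine screen is not used to identify them

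*Protocol article*

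**What the plan says.** **Eligibility.** Under Exclusion Criteria, the protocol article rules out people "currently on buprenorphine MOUD treatment". It does not mention buprenorphine taken outside treatment. Under Inclusion Criteria, candidates need a "desire to start buprenorphine treatment" and "a judgment that the subject is appropriate for participation by the treating clinician". Study Population and Sample Size adds: "No additional criteria will be applied by the investigator to ensure the study population will be representative of all eligible participants".

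**Baseline visit.** Study Procedures and Assessments re-checks the listed criteria: "At baseline, if participants still meet all inclusion and exclusion criteria, study staff will provide them with a phone". At the same visit, "Additionally, a UDS will be performed, and the Clinical Opiate Withdrawal Scale (COWS) will be used". Table 1 confirms a urine screen and a Timeline Followback at week 0. Medical and Medication History collects medication start and stop dates, opioid use history and prior experience with medication for OUD.

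**Analysis.** Under Primary End Points, initiation success is summarised by week-1 attendance and by the proportion with initiation-related adverse events. Adherence is self-report confirmed by urine screen. The urine data are averaged over each participant's "proportion of total urine samples testing positive for buprenorphine or norbuprenorphine over the 4-week study". The compensation list under Confidentiality counts five urine samples, which matches weeks 0 to 4 in Table 1. None of the primary, secondary or exploratory analyses divides participants by their day-0 buprenorphine result.

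**The concern.** Textbox 1 states the primary objectives as the effect of PEAR-002b on home initiation success and on adherence, plus its acceptability. The week-1 function of the product is to guide a person through starting the medication. The Introduction says that a successful start requires the patient to be in mild to moderate withdrawal first. Someone already taking buprenorphine is not making that transition in the sense the study intends.

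If such a person attends at week 1 without precipitated withdrawal, the plan counts a successful initiation. If the later urines are positive, it counts adherence, although the person was positive before the study began. The Discussion says the data may inform larger studies, so an initiation rate that mixes new starters with people already exposed could be carried forward as a planning figure.

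**Working it through.** The article states no rate, power or calculated sample size for this point, so there is no figure to reproduce. The check has two parts.

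**1. Can such a person enter?**
- The exclusion names current treatment only. A non-prescribed user is not in treatment and passes.
- Wanting to start treatment is compatible with already using the drug without a prescription.
- The baseline re-check covers only the listed criteria, and the investigator adds none.
- The one discretionary filter is the treating clinician's judgment, which is not tied to buprenorphine exposure.

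So entry is possible as written. The article does not say how often it would happen.

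**2. What could it do to the reported figures?**

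Inputs from the article: 10 participants; five urine samples, one of them at baseline.

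Assumptions: *k* = 2 of the 10 are already exposed and positive on day 0. New starters are negative on day 0 and are positive at a fraction *q* = 0.70 of the four later samples. Exposed people are positive at a fraction *q′* of the later samples. All samples are given.

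Individual adherence:
- baseline left out: new starter *q*; exposed *q′*
- baseline counted: new starter 4*q*/5; exposed (1 + 4*q′*)/5

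Group mean = [(10 − *k*) × new + *k* × exposed]/10.

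| Baseline sample | Exposed people later | New starter | Exposed | Mean, k = 0 | Mean, k = 2 | Shift |
|---|---|---|---|---|---|---|
| Left out | same rate, 0.70 | 0.70 | 0.70 | 0.70 | 0.70 | 0 |
| Counted | same rate, 0.70 | 2.8/5 = 0.56 | 3.8/5 = 0.76 | 0.56 | (4.48 + 1.52)/10 = 0.60 | 4 points |
| Left out | always positive | 0.70 | 1.00 | 0.70 | (5.60 + 2.00)/10 = 0.76 | 6 points |
| Counted | always positive | 0.56 | 1.00 | 0.56 | (4.48 + 2.00)/10 = 0.648 | 8.8, about 9 points |

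The second row is a purely mechanical effect. If the baseline sample counts, a day-0-negative participant cannot exceed 4/5 = 80%, while an exposed one can reach 100%. Each exposed person then adds 2 points to the mean whatever *q* is, even with identical later adherence.

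Sensitivity to *q* with *k* = 2 and exposed people always positive:
- *q* = 0.5: shift of 10 points (baseline left out, 0.50 to 0.60) or 12 points (counted, 0.40 to 0.52)
- *q* = 0.9: shift of 2 points (left out, 0.90 to 0.92) or 5.6 points (counted, 0.72 to 0.776)

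**Attendance.** Assume 0.70 in new starters and two exposed people. If they attend equally, the rate stays at 0.70. If they attend at 0.9, it is (5.6 + 1.8)/10 = 0.74. If they always attend, it is (5.6 + 2.0)/10 = 0.76.

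For scale, the exact 95% confidence interval for 7 of 10 is 0.35 to 0.93.

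**The case against.** **The article has partial filters.** The clinician's judgment, the wish to start treatment and the medication and substance-use histories may screen out or at least reveal some non-prescribed users. This stands, and it is why the point is that such people can enter, not that they do. None of these filters is tied to the day-0 urine result.

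**Recently stopped treatment.** A reader might infer that people who stopped prescribed buprenorphine shortly before enrolment are wrongly admitted, the more so because "no participation in investigational drug trials within the past 30 days" gives a look-back for trial participation and buprenorphine has none. The documents do not support this. The study does not require buprenorphine-naive participants, and a person who stopped still has to restart. The window concerns investigational drug trials and does not imply a missing buprenorphine washout.

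**Size and direction.** A reader might infer that each exposed participant moves attendance by 10 points, or that every error favours the product. Ten points is simply 1/10, a maximum reached only if that person's outcome would certainly have been the opposite. Attendance is not a urine result, so prior exposure acts on it only indirectly, and nothing in the article shows that exposed people attend more or have fewer adverse events.

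**Detail left to documents not shown.** A derived flag could sit in an analysis plan. That is fair for the mechanics. But the article sets out its eligibility criteria and writes out its primary summaries, and as written these pool both kinds of participant.

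**Small descriptive study.** There is one arm, no test and no threshold, and the limitations already admit the small sample and missing comparator. The harm is therefore to interpretation, not to an error rate.

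**Conclusion.** The point holds in a limited form. As written, non-prescribed buprenorphine users can enter and be counted in the initiation and adherence results, and the day-0 urine screen that could identify them is not used for this.

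No prevalence is given, so no bias has been shown to occur. Under the assumptions of two exposed people in 10 and a 70% later positive rate in new starters, mean adherence shifts by between 0 and about 9 points. The answer depends on whether exposed people really are positive more often later, and on whether the baseline sample belongs to the total, which the wording leaves open. Attendance does not move unless exposed people attend more often. These shifts are small beside the sampling uncertainty with 10 participants. The reason to act is that the remedy is cheap and makes clear what the primary measures describe.

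**What to change.** 1. Derive a day-0 flag from the baseline urine screen: positive or negative for buprenorphine/norbuprenorphine. Use the baseline Timeline Followback and the medication history as supporting information.
2. Report week-1 attendance, initiation-related adverse events and urine-confirmed adherence for day-0-negative participants. List the day-0-positive participants separately, and keep the all-participant result alongside.
3. State that the adherence proportion uses only post-baseline samples (weeks 1 to 4). This removes the mechanical 2 points per exposed person.

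The cost is one derived variable and a few lines of text; no new test or visit is needed. The downside is that the new-starter group may be slightly smaller than 10, with correspondingly wider uncertainty. Whether to change the eligibility wording as well is a trade-off for the investigators, since a narrower criterion could slow recruitment and make the sample less representative.
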